## Sample size and power calculation

The sample size calculation for the binary primary outcome is based on testing for superiority in a parallel group clinical trial. As only case reports have been published on rapid micro-induction, we expect a success rate of 95% in the experimental arm based on the opinion of two addiction psychiatry experts familiar with the method. We expect a success rate of 10% in the control arm, as most participants in the arm are anticipated to experience moderate to higher levels of withdrawal, which is defined as having a COWS score of ≥ 13. A difference of such a magnitude, 85%, is deemed clinically meaningful. Using G*Power 3.1 software, the minimum required sample size to power a Fisher’s exact test to detect this difference between the two arms with a type I error of 0.05 and a type II error of 0.1 will be 12 (6 in each arm). Adjusting for an attrition rate of 10% (participants with incomplete COWS data, participants who have discontinued the treatment they were randomized, and participants who have discontinued both treatment and data collection procedures), the required sample size is 14. We aim for a sample size of 50 (25 each arm), as a larger sample size is not feasible due to cost and constraints.

## Safety, treatment discontinuation, and study discontinuation

### Safety

Safety will be assessed by the appearance of adverse events (AEs) and serious adverse events (SAEs). AEs and SAEs will be monitored throughout the study. An AE is defined as any untoward medical occurrence in a participant, administered a study intervention, which does not necessarily have a causal relationship with this intervention [34]. A SAE is defined as any untoward medical occurrence meeting one of the following criteria at any dose: results in death, is life-threatening, requires inpatient hospitalization or prolongation of existing hospitalization, results in persistent or significant disability or incapacity, or is a congenital anomaly or birth defect. All AEs and SAEs will be documented accordingly on the adverse event report form, and will be reported to the clinical trial’s Data Safety and Monitoring Board (DSMB). All SAEs will be reported to the Sponsor-Investigator and Health Canada.

### Treatment discontinuation and study discontinuation

Participants are free to discontinue the treatment arm they were randomized to (treatment discontinuation), or the treatment they were randomized to and any data collection procedures (study discontinuation). Discontinuation may occur at any time without participants having to provide any reason and without prejudice to their medical care. Discontinuation from treatment or study may occur in the following circumstances, but not limited to: participant’s request, severe adverse reactions/events and/or other safety reasons, violence against treatment team without convincing evidence of mental illness like psychosis or delirium, and criminal behaviour with resulting imprisonment during the study period. All discontinuations from treatment or study will be documented on the CRF. Such participants will be considered failures of the primary outcome.

If participants discontinue the treatment they were randomized to (treatment discontinuation), they will be offered the other parallel treatment. This will be determined by the physician in charge in consultation with the patient*.* In order to reduce the amount of missing or incomplete data from such participants, research staff will continue to collect data from the participants if they allow them to do so.

If participants discontinue from the study (study discontinuation), the research staff will not collect data from them, and CPAS physicians will follow-up with appropriate treatment options.

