### Primary outcome

The primary outcome is the completion of buprenorphine/naloxone with low levels of withdrawal. Success on the primary outcome is defined as the following: participants who remain in treatment until they have received a total dose of ≥ 8 mg of buprenorphine/naloxone within a 24-h period (successful induction), and score ≤ 12 on the COWS (low levels of withdrawal) from baseline to when they reach that dose [29]. The COWS will be administered at baseline, every 1.5 h during the abstinence period (control arm only), and throughout the induction process for both arms (days 1 to 2 of the experimental arm, and day 1 of the control arm)—specifically, immediately before each dose of buprenorphine/naloxone, and 1 to 1.5 h after each dose of buprenorphine/naloxone. Our primary hypothesis is that there will be a significantly higher number of participants in the rapid micro-induction arm who will be successfully induced onto buprenorphine/naloxone with low levels of withdrawal, compared to participants in the standard induction arm.

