## Data analysis

All analyses will be conducted with both intention-to-treat (ITT) and per-protocol (PP) methods. Participants who discontinue the treatment arm they were randomized to (includes switches to the other arm) will be considered as failures of the primary outcome.

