### Primary outcome

The primary outcome will be assessed in a binary fashion: participants need to fulfill both criteria (successful induction and low levels of withdrawal) in order to be successful with the primary outcome. Outlier COWS scores will be checked and confirmed with the clinical records on an ongoing basis by the study coordinator. Effort will be made by the study team to avoid missing COWS scores during the study. In case of missing scores, multiple imputation will be used to impute the missing variables, and sensitivity analysis will be performed by once assigning failure to all the missing COWS score and then success to them, then describing and explaining the impact on the results. Fisher’s exact test will be used to compare two groups with a significance level set at 0.05. To demonstrate the effect size, we will use both unadjusted and adjusted odds ratios with 95% confidence intervals using logistic regression. In the latter, effect size will be adjusted for age, gender, and baseline COWS score in addition to allocated arm. Adjustment for baseline covariates will improve the sensitivity of the comparison.

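### The failure rule for discontinuation has no time limit, so a participant who meets the primary success definition and then stops or switches during the remaining treatment days is scored both success and failure

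*Protocol article*

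**What the plan says.** The protocol article scores the primary outcome in four places.

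- **Outcomes and assessments, Primary outcome.** Successful induction applies to "participants who remain in treatment until they have received a total dose of" at least 8 mg within 24 h. The withdrawal criterion is a COWS score of 12 or less, "low levels of withdrawal) from baseline to when they reach that dose". Both criteria end when the dose is reached.
- **Data analysis, Primary outcome.** The outcome is binary, and "participants need to fulfill both criteria (successful induction and low levels of withdrawal) in order to be successful with the primary outcome". No third criterion is added.
- **Treatment discontinuation and study discontinuation.** "Discontinuation may occur at any time without participants having to provide any reason". The section then states: "All discontinuations from treatment or study will be documented on the CRF. Such participants will be considered failures of the primary outcome".
- **Data analysis, opening paragraph.** "Participants who discontinue the treatment arm they were randomized to (includes switches to the other arm) will be considered as failures of the primary outcome".

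The treatment sections supply the timing. In the rapid micro-induction arm, induction is complete by the end of day 2 and day 4 is the last treatment day. In the standard arm, the COWS schedule places induction on day 1 (which may exceed 24 h) and day 3 is the last treatment day. Retention is a separate secondary outcome, assessed by prescription pick-up on day 7.

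**The concern.** The outcome definition closes at the moment of induction, whereas the discontinuation rule never closes. Between the two lie about two scheduled treatment days in each arm. A participant who reaches the dose with low COWS scores throughout and then stops, or moves to the other arm, on one of those days satisfies both rules, and the rules give opposite answers.

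Three things are at stake. First, individual primary results are not determined by the text. In an open-label trial, the rule should be fixed before anyone sees which participants it affects. Second, the literal failure rule makes the endpoint partly a measure of staying in treatment after induction, although the objective is successful induction with low withdrawal and retention is measured separately. Third, at equal discontinuation rates the rule falls mainly on the experimental arm, because that arm is expected to hold most of the successes. The estimated success rates and the odds ratios promised in the analysis section therefore depend on which rule is applied.

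**Working it through.** **Step 1. Reproduce the plan's figure.** Inputs from the sample size section: success 95% vs 10%, type I error 0.05, type II error 0.1, Fisher's exact test, 6 per arm. Enumerating the two binomial distributions gives one-sided power 0.831 at 5 per arm and 0.945 at 6, so 6 per arm (12 in total) is reproduced with a one-sided test. Two-sided power is 0.774 at 6 and 0.919 at 7. The article does not state sidedness, and it is immaterial at the planned 25 per arm. The attrition step also reproduces: 12 / (1 − 0.10) = 13.3, rounded up to 14. The planned difference is 95 − 10 = 85 points, and the planned odds ratio is (0.95/0.05) / (0.10/0.90) = 171.

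**Step 2. Set the rules side by side.**

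| Participant | Primary outcome definition | Discontinuation rule |
|---|---|---|
| Stops before 8 mg within 24 h | Failure | Failure |
| Reaches the dose, COWS at most 12 throughout, completes treatment | Success | Not applicable |
| Reaches the dose, COWS at most 12 throughout, then stops or switches (about days 3-4 experimental, 2-3 control) | Success | Failure |

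Only the third row is in conflict. For ordinary stops before completion the failure rule adds nothing, because the definition already requires staying in treatment until the dose is reached. There it serves mainly to make explicit that early switchers are failures.

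**Step 3. Illustrate the size.** The documents give no rate for the third row. Let d be the assumed share of qualifying participants who later discontinue, equal in both arms. Under the literal failure rule the success rates are 95%(1 − d) and 10%(1 − d), the difference is 85(1 − d) points, and the odds ratio follows from those two rates.

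| d | Experimental | Control | Difference (points) | Odds ratio |
|---|---|---|---|---|
| 0 | 95% | 10% | 85 | 171 |
| 5% | 90.25% | 9.5% | 80.8 | about 88 |
| 10% | 85.5% | 9.0% | 76.5 | about 60 |
| 20% | 76.0% | 8.0% | 68.0 | about 36 |

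Example at 10%: (0.855/0.145) / (0.09/0.91) = 5.897 / 0.0989 = 59.6. In participants, expected successes are 0.95 × 25 = 23.75 and 0.10 × 25 = 2.5, so 10% reclassifies about 2.4 in the experimental arm and 0.25 in the control arm.

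**Step 4. Effect on the test.** Two-sided Fisher power at 25 per arm stays above 0.999 for d up to 20%, including when only the experimental arm is affected. In observed counts, 24/25 vs 2/25 gives p = 1.2 × 10⁻¹⁰ and 21/25 vs 2/25 gives p = 7 × 10⁻⁸. With a much smaller effect, one participant can matter: 17/25 vs 9/25 gives p = 0.046, and 16/25 vs 9/25 gives p = 0.089. Those counts are illustrative and far from the planned rates.

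**The case against.** The best defence is that the authors meant discontinuation before induction is complete. Those who discontinue are offered the other treatment, which is another induction method and makes most sense while induction is unfinished. The primary analysis section restates only the two induction criteria. This reading is plausible and is probably what was intended. But the text places no limit on when discontinuation counts, covers every discontinuation from treatment or study, and repeats the rule in the analysis section without narrowing it.

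A second defence is that counting discontinuation as failure is a recognised composite approach and, by removing mainly experimental successes, is conservative here. That stands. The stricter rule would be legitimate if it were part of the definition, but it is not.

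Three stronger readings are tempting and are not supported:

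- **The conflict runs to day 7.** Study discontinuation is defined as leaving the randomized treatment together with data collection. By day 5 randomized treatment has ended in both arms, so someone who declines further contact then does not clearly fall under the rule. The clear window is about two days per arm.
- **The protocol's own 10% attrition measures the effect.** That figure combines incomplete COWS data, treatment discontinuation and study discontinuation. COWS is collected only through induction, so the figure is not a post-completion rate.
- **The trial's conclusion is at risk as planned.** At 95% vs 10% the test result is the same under either rule.

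**Conclusion.** The point holds as a contradiction between two stated rules, limited to participants who qualify and then discontinue or switch during the remaining treatment days. It is not a matter of detail left to an analysis plan, because both rules are explicit and they disagree.

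Its weight lies in the definition and estimation of the primary endpoint rather than in power. The planned difference would move from 85 to between 80.8 and 68.0 points, and the odds ratio from 171 to between about 88 and 36, for assumed equal post-completion discontinuation of 5% to 20%. These rates are assumptions, since no figure is given. The planned sample size is unaffected. The test is unaffected at the planned rates, but the 95% rests on the opinion of two experts, and with a much smaller true effect a single reclassified participant could decide significance.

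**What to change.** Before analysis, reconcile the outcome definition, the discontinuation section and both parts of the Data analysis section. The change most consistent with the stated definition is to limit the failure rule in the discontinuation section and in the opening of Data analysis. Suggested wording: participants who discontinue the assigned treatment (including by switching arms) or the study before meeting the induction criterion are failures of the primary outcome; discontinuation after that point does not alter the primary result and is reflected in the day-7 retention outcome.

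If the sponsor intends the stricter rule, it should instead be written into the primary outcome definition as a further condition, with the day up to which it applies, and the analysis section should list it alongside the other two criteria.

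Either way this is a scoring clarification that leaves treatment and clinical management untouched. It costs a clause of text and needs no new data and no change to the sample size.

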### Secondary outcomes

The secondary outcomes are treatment retention, illicit drug use, self-reported drug use behaviour, craving, pain, physical health, safety, and client satisfaction.

Treatment retention will be assessed by buprenorphine/naloxone prescription pick-up on day 7.

Illicit drug use will be assessed by urine drug screens, which will analyze for the presence of cocaine, opioids including methadone, buprenorphine, hydromorphone, oxycodone, morphine, heroin, and fentanyl, benzodiazepines, amphetamines, and methamphetamine. Urine will be collected at screening, baseline, and after induction has been completed (day 3 of the experimental arm, and day 2 of the control arm).

Self-reported drug use behaviour will be assessed by the Treatment Outcome Profile (TOP) at baseline, and after induction has been completed (day 3 of the experimental arm, and day 2 of the control arm). The TOP is a 20-item instrument designed to assess and monitor substance misuse by measuring four different domains (substance use, health, crime and social functioning) and includes thirty-eight frequency, rating scale and period prevalence measure [30].

Craving and pain will be measured by numeric rating scales (NRS) at baseline, days 1 to 2 of the experimental arm, and day 1 of the control arm. The NRS for craving and pain will be administered every time the COWS is administered. The NRS presents the participant a rating scale which represents the spectrum of pain or craving: the left end indicates no pain or craving while the right end indicates extreme pain or craving [31]. Participants rate their pain or craving from 0 to 10.

Physical health will be assessed by the health section of the Opiate Treatment Index (OTI) at baseline. The OTI is a structured interview designed to provide a measure of the effectiveness of drug treatments, by measuring six outcomes: drug use, HIV risk-taking behaviour, social functioning, criminality, health status, and psychological functioning [32]. Only the health section of the OTI will be used; the health section is composed of items addressing signs and symptoms in major organ systems and injection-related health problems.

Safety will be assessed by the appearance of adverse events (AEs) and serious adverse events (SAEs), which will be recorded on the CRF. AEs and SAEs are defined in “Safety” section.

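### Adverse-event collection can stop after removal for safety, and neither stated analysis shows switchers' harms by the regimen they were receiving

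*Protocol article*

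**What the plan says.** The section *Treatment discontinuation and study discontinuation* defines two exits and gives them one shared list of reasons: "Discontinuation from treatment or study may occur in the following circumstances, but not limited to: participant’s request, severe adverse reactions/events and/or other safety reasons". Nothing in it says which exit follows from which reason.

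- **Treatment discontinuation.** Of these participants the section says "they will be offered the other parallel treatment", and that "research staff will continue to collect data from the participants if they allow them to do so".
- **Study discontinuation.** This is defined as leaving both the allocated treatment and the data collection procedures. The consequence is: "If participants discontinue from the study (study discontinuation), the research staff will not collect data from them".

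The *Safety* section says "AEs and SAEs will be monitored throughout the study". It also requires every AE and SAE to be documented and sent to the monitoring board, and every SAE to go to the sponsor-investigator and the regulator.

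The *Data analysis* section says "All analyses will be conducted with both intention-to-treat (ITT) and per-protocol (PP) methods". Safety is one of the outcomes this covers: "The secondary outcomes are treatment retention, illicit drug use, self-reported drug use behaviour, craving, pain, physical health, safety, and client satisfaction". The only rule given for switchers is that they count as failures of the primary outcome.

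**The concern.** Safety is half of the stated aim, and the article presents the trial as the first randomised comparison of this method. Two rules weaken the safety comparison.

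First, a participant taken off study because of "severe adverse reactions/events and/or other safety reasons" falls under the same no-data rule as one who simply withdraws. The people whose safety follow-up matters most can then be the ones for whom it stops.

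Second, crossover is part of the design, and the regimens differ in a way that matters for harms: only rapid micro-induction includes protocol hydromorphone. An event in a control participant who has switched to micro-induction is counted against standard induction under ITT. An event in a micro-induction participant who has switched to standard induction is counted against micro-induction. Neither stated analysis shows a reader how many events occurred on each regimen.

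**Working it through.** **Inputs from the article.** 25 per arm and 10% attrition (*Sample size and power calculation*); the AE form is last scheduled on day 3 for control and day 4 for experimental (Table 3). The article gives no AE rate, SAE rate, switching rate or count of safety exits. The nearest figure is the 10% attrition, which reproduces as stated: 12 / 0.9 = 13.3, rounded up to 14. It pools incomplete COWS data, treatment discontinuation and study discontinuation, so it is not a count of safety exits or of switchers.

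**Step 1: what is at risk after removal for safety.**

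| Item | Rule in the article | Collected? |
|---|---|---|
| Event that triggers removal | All AEs and SAEs documented and reported (*Safety*) | Yes |
| The discontinuation itself | Documented on the CRF | Yes |
| Later course, if only treatment is stopped | Collection continues if the participant allows | Yes, with agreement |
| Later course and later events, if taken off study | No collection by research staff | No |

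Only the last row conflicts with monitoring throughout the study.

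**Step 2: where a switcher's later event is counted.**

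| Switch | Regimen at onset | ITT | PP as usually understood |
|---|---|---|---|
| Control to experimental | Micro-induction | Standard induction | Left out |
| Experimental to control | Standard induction | Micro-induction | Left out |

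The article does not define PP, so the last column is an inference.

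**Step 3: scale.** One event in 25 is 1/25 = 4 percentage points of an arm's rate.

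**Step 4: illustrations under assumed rates.** Take true event rates of 20% on micro-induction and 4% on standard induction, a difference of 16 points by regimen. Let *s* of 25 control participants switch and take on the 20% rate in place of the 4%. The ITT control rate is [(25 − s) × 0.04 + s × 0.20] / 25.

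- s = 1: 1.16 / 25 = 4.64%, ITT difference 15.4 points.
- s = 5: 1.80 / 25 = 7.20%, ITT difference 12.8 points.

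The ITT difference is thus 0.6 to 3.2 points below the difference by regimen.

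The direction is not fixed. Suppose instead that switchers add the second regimen's risk to the first, and count expected events per participant. Five control switchers give (25 × 0.04 + 5 × 0.20) / 25 = 0.08, a difference of 12.0 points. Five experimental switchers give (25 × 0.20 + 5 × 0.04) / 25 = 0.208, a difference of 16.8 points. One is below 16 and the other above.

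For uncollected follow-up, take the extreme case in which all 50 × 0.10 = 5 attrition cases fall in one arm and contribute nothing. The arm then has 20 observed. With zero events, the 95% upper bound 1 − 0.05^(1/n) rises from 11.3% (n = 25) to 13.9% (n = 20). The chance of seeing at least one event of true rate 5%, 1 − 0.95^n, falls from 0.72 to 0.64. The real loss would be smaller, because what happens before exit is recorded.

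**The case against.** The strongest reply has four parts.

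1. **The events are recorded.** The triggering event happens on study and must be documented and reported, and a severe event may lead only to treatment discontinuation, after which collection can continue. This stands. A reader might infer that serious harms are lost; the article does not support that. Only the later course and later events are exposed.
2. **Study discontinuation means leaving data collection.** That no data then follow largely restates the definition, and it respects withdrawal. This stands for participants who choose to go. It does not cover the listed reasons that need not come from the participant, safety among them.
3. **Safety sets belong in an analysis plan that is not shown.** This is fair, and the absence of a safety set is not the point here. The point is a sentence in the article that fixes ITT and PP for all analyses, with safety among the listed outcomes, in a design that offers crossover.
4. **Direction and size are unknown.** This stands. A reader might infer that the rules make rapid micro-induction look safer, since most controls are expected to have more than low levels of withdrawal and might switch more often. But switching is offered both ways and no rates are given. A reader might also move two events between arms and report 2/25 + 2/25 = 16 points. That assumes both switchers have an event after switching and holds both denominators at 25, neither of which the article supports.

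Grouping by regimen at onset also has its own faults: it gives up randomisation, and effects carried over from the first regimen can be credited to the second. It can supplement the as-randomised table but not replace it.

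**Conclusion.** The point holds in limited form.

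- The article does not distinguish removal for safety from withdrawal of consent to data collection. Later AE/SAE information may therefore go uncollected, contrary to its own statement on monitoring.
- Neither stated analysis shows harms by regimen received. For ITT this follows from the text. For PP it assumes the usual meaning.

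No direction or amount of distortion can be claimed. The only figure that needs no assumed rate is the scale: one event is 4 percentage points of a 25-person arm, so one misplaced or unfollowed event would be visible in the results. This is a cheap improvement; it does not threaten the primary analysis.

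**What to change.** 1. **Data analysis.** Add a table of AEs and SAEs in all treated participants by the regimen being received at onset, beside the as-randomised table. Count the control abstinence period as standard induction, since the article dates the start of that induction from it. Note under the table that the grouping is not randomised and that carry-over may misplace events.
2. **Safety and discontinuation sections.** Reconcile them so that removal for safety does not by itself end AE/SAE data collection. Collection continues over the same AE-form schedule as for other participants (Table 3: to day 3 in control, day 4 in experimental) unless the participant withdraws consent to data collection.
3. **Leave unchanged** what treatment is offered after a safety exit. This is a change to data collection and reporting only.

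**Cost.** Two wording changes, one extra table and a little more AE follow-up for a few participants. The table needs regimen start and stop times and AE onset times. The article says the CRF holds the type, duration and reason for medications and all discontinuations, but does not say that it holds those times, so the form should be checked.
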